### Identification of eligible patients

All ambulatory patients with suspected DVT attending the ED will undergo risk stratification, blood investigation and subsequent complete lower limb duplex compression ultrasound (CUS), in line with standard practice. Prior to ultrasonography, all patients with suspected DVT will be provided with a patient information sheet outlining the trial protocol.

Patients will be managed in an ED thrombosis clinic the same day, where they will be further counseled regarding diagnosis and treatment options. The presence of isolated thrombus in any of the peroneal, soleal, gastrocemial, or tibial veins on duplex CUS detected by an accredited vascular technician, will constitute the diagnosis of distal DVT. Patients with confirmed distal disease will be screened for eligibility by a trained researcher. Inclusion/exclusion criteria are documented below. Only patients able to provide written informed consent will be approached for inclusion. Demographic data will be collected on case report forms, including risk factors (permanent and temporary), provocation, baseline blood tests and examination findings.

#### Inclusion criteria

• Aged 16 or above

• Symptomatic attendance to the Emergency Department with atraumatic leg pain and/or swelling as the principal complaint

• Objective diagnosis of distal deep vein thrombosis by duplex vascular ultrasound

#### Exclusion criteria

• Hospitalised patients (all inpatients)

• Long term therapeutic anticoagulation

• Associated confirmed venous thromboembolic disease (Proximal leg DVT, PE or central vein thrombosis)

• Contraindication to anticoagulation (presence of active bleeding, recent haemorrhagic stroke or upper gastrointestinal bleed)

• Active cancer

• Any other indication for anticoagulation according to national/local guidance: prior confirmed and treated above knee DVT/PE, antiphospholipid syndrome or symptomatic inherited thrombophilia.

• Pregnancy

• Chronic non propagating thrombus

• Previous enrollment to the ACT trial

### Randomization technique

Randomization will occur after patient consent has been taken. Participating patients will be assigned to one of two groups by a remote, computerized, web-based randomization sequence, constructed with variable permuted block size. Group A will be allocated to receive therapeutic anticoagulation with standard pharmacotherapy, group B to receive conservative management. All patients will be briefed in person and writing regarding the clinical signs of extending DVT/PE and advised to contact the trial team or return to the ED with any concerns.

### Blinding

This is an open-label study. Although previous trials have used 'sham' anticoagulant clinics we feel use of placebo and frequent hospital visits to maintain blinding would be potentially unethical and deleterious to recruitment. Complications in the context of warfarinization also need urgent treatment and an unblinding protocol would naturally delay this.

All ultrasonographers will be blinded to allocation for repeat scans. Clinical outcome measures are primarily objective, which should minimize the risk of measurement bias.

### Patient follow-up procedures

Patients will return at 7 and 21 days for follow-up duplex CUS and clinical review. Vascular radiology technicians will be blinded to treatment allocation for all scans. Propagation of DVT to the level of the popliteal vein (above the trifurcation) at any point post randomization will be considered as proximal extension and result in immediate therapeutic anticoagulation. Patients will be clinically reviewed and outcome data collected when they attend for repeat CUS. Worsening symptoms in the context of non-propagation above the trifurcation will be assessed carefully and further investigations will be dictated by clinical need.

At the end of the 3-month treatment period all subjects will be followed up via medical record review and structured telephone interview. An ED appointment will be arranged if any queries or clinical concerns persist. All patients will be encouraged to continue wearing compression stockings daily for 2 years, as per current evidence [38]. Suspicion of pulmonary VTE at any stage will be investigated as per current practice and confirmed by Prospective Investigation Of Pulmonary Embolism Diagnosis (PIOPED) reported V/Q scan or computed tomography (CT)-pulmonary angiography [39]. Any patient diagnosed with pulmonary VTE will receive immediate therapeutic anticoagulation as per current practice. Out of normal working hours, patients will be advised to attend the ED with any concerns, where a protocol for investigation of suspected pulmonary embolism in ambulatory patients is already standard practice.

Final clinical review and data collection will occur at 2 years post inclusion, regarding the incidence and severity of post thrombotic syndrome and the incidence of DVT recurrence in all patients. The diagnosis and severity of PTS will be assessed using the standardized scoring system validated by Villalta et al. [40].

### Patient outcome measures

As an external pilot study, the primary endpoints for the trial will constitute measures of feasibility only. A successful pilot RCT seeks to collect data regarding process, resources, management and scientific data [41]. Feasibility outcomes have been designed to reflect this. Clinical measures of treatment effect and safety will be recorded as secondary outcomes, in order to inform further sample size calculations and data inference for potential future multicenter research.

Primary feasibility outcomes are: incidence of the index condition, the proportion of eligible patients within the screening cohort, recruitment rate for those deemed eligible, allocation crossover and short-term compliance with the study protocol.

Secondary outcomes are: combined incidence of thrombus propagation to the popliteal vein, DVT recurrence, development of pulmonary embolism or VTE related sudden death during the 3-month intervention period; incidence of major and minor bleeding episodes during the 3-month treatment period; incidence of post-thrombotic leg syndrome at 2 years; and incidence of VTE recurrence at 2 years.

Outcome measures will be defined using the following tools: DVT recurrence or development of pulmonary embolism will be confirmed by objective diagnostic criteria, either via repeat CUS in the presence of worsening symptoms or PIOPED reported ventilation-perfusion scan or CT pulmonary angiogram in the presence of new chest symptoms [39]. Any cases of sudden death during the interventional phase of the trial will be assessed by a panel of experts blinded to treatment allocation, including a Professor of Emergency Medicine, Consultant Hematologist and Consultant Respiratory Physician. A consensus decision will be required regarding VTE as the principal cause of death.

Major bleeding episodes will be defined as standardized in 2005 by Schulman et al.: clinically overt and associated with a fall in hemoglobin of 20 g/l, resulting in the need for transfusion of two or more units of red cells, involving a critical site, or fatal [42]. Minor bleeding episodes will be subcategorized as per Schulman et al. in 2009 into clinically relevant, or nuisance bleeding [43].

Post-thrombotic syndrome will be diagnosed and numerically graded using the validated and internationally adopted Villalta scale [40].

### Withdrawal, allocation crossover and protocol violation

Participants withdrawing from the study voluntarily will be included in the intention to treat analysis. Allocation crossover will be deemed to occur if patients allocated to conservative treatment are prescribed full dose therapeutic anticoagulation for > 5 days at any stage during 3-month follow-up, or patients allocated to anticoagulation have therapy withheld for > 5 days.

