## Background

Venous thromboembolic (VTE) disease is an international, topical and costly healthcare burden. Incidence rates are equivalent to that of stroke within the western hemisphere [1] and disease consequences can be as severe. Recent studies addressing prognosis provide a stark reminder of continuing poor outcome, quoting a 15% mortality rate at 3 months post diagnosis for VTE involving the pulmonary vascular tract [2]. Outcome from VTE confined to the lower extremities fares little better, with a reported short-term all-cause mortality between 7% and 15% [3]. Observational data suggests reduced survival compared to control subjects after first episode of symptomatic deep vein thrombosis. This trend has been shown to persist for up to 8 years post diagnosis [4]. Clinical research demonstrating poor outcome has led to a national focus on early diagnosis and active prevention, with the creation of guidelines from both the UK Health Technology Assessment (HTA) group and the National Institute of Clinical Excellence (NICE) within the last decade [5,6].

Despite the large body of research on VTE, controversy still remains regarding many aspects of therapeutic clinical practice. One such area is that of distal deep vein thrombosis (DVT), a condition previously thought to be of limited clinical significance. There are multiple epidemiological studies suggesting distal thrombi constitute approximately 50% of objectively diagnosed lower limb disease in symptomatic ambulatory patients [7-9]. This proportion may be even higher in asymptomatic disease or hospitalized patients [10]. However, the benefits of intervention in distal disease remain poorly researched, with conflicting international guidance on investigation and treatment.

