### Statistical analysis

As a feasibility study, principal analysis will focus on the incidence of distal DVT as the index condition within the screening cohort and the proportion of eligible patients willing to participate in the trial. Protocol violations and allocation crossover rate will also be assessed within the two groups to determine the feasibility of maintaining treatment allocation within each cohort for the duration of the study period. Binomial confidence intervals will be estimated for all proportions using the Wilson score exact method.

The predefined criteria for assessing success of feasibility will constitute the following: (1) index disease incidence > 5% within the screening cohort, (2) > 70% recruitment rate within eligible participants and (3) < 25% protocol violation rate.

The secondary analysis will be a comparison of anticoagulation versus conservative treatment for prevention of the secondary clinical endpoint following the 'intention to treat' principle. A further 'per protocol' analysis of all clinical endpoints will take place excluding all withdrawals, allocation crossovers and protocol violations. Proportions will be compared for statistical significance using Fisher's exact test and a further descriptive analysis made of the individual components forming the composite primary outcome. An estimate will be made with 95% confidence interval of absolute risk reduction. Together with the primary feasibility outcomes, this data will allow estimation of the number of sites, duration of recruitment and resources needed to conduct the definitive multicenter study.

Further intention to treat analyses of secondary and tertiary endpoints occurring within the two groups will be compared using Fisher's exact test. All significance tests will be two sided.

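### VTE recurrence at 2 years is fixed as a crude proportion with withdrawals kept in the denominator, so incomplete follow-up may lower the rate and, if loss differs by arm, distort the comparison

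*Protocol article*

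**What the plan says.** Four statements in the protocol article bear on this point.

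- **Population.** Withdrawal, allocation crossover and protocol violation: "Participants withdrawing from the study voluntarily will be included in the intention to treat analysis".
- **Method.** Statistical analysis, on the main clinical endpoint: "Proportions will be compared for statistical significance using Fisher's exact test and a further descriptive analysis made of the individual components". On the other endpoints: "Further intention to treat analyses of secondary and tertiary endpoints occurring within the two groups will be compared using Fisher's exact test". The main comparison also carries an effect estimate: "An estimate will be made with 95% confidence interval of absolute risk reduction".
- **Outcome.** Patient outcome measures lists "incidence of VTE recurrence at 2 years" among the secondary outcomes, next to post-thrombotic syndrome at 2 years.
- **Follow-up.** Patient follow-up procedures sets visits at 7 and 21 days, a record review and telephone interview for all subjects at 3 months, and a final review at 2 years. Nothing is scheduled in between.

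Statistical analysis adds a second analysis set: "A further 'per protocol' analysis of all clinical endpoints will take place excluding all withdrawals, allocation crossovers and protocol violations".

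**The concern.** Fisher's exact test needs each included patient to be either an event or a non-event. For a patient who withdraws event-free at, say, month 8, there are three ways to fill the cell: count a non-event, assign an assumed outcome, or drop the patient. Dropping goes against the withdrawal rule. None of the three uses the event-free time that was observed.

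This matters most for 2-year recurrence, because 21 months pass without a planned contact. Treatment is open-label, and only one arm has warfarin and anticoagulant clinic visits, so loss could differ by arm. The article says that the clinical outcomes are recorded to inform the design of later research, so a 2-year rate that is too low could be carried forward.

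**Working it through.** The plan gives no figure for 2-year recurrence, loss or death, so there is nothing of its own to reproduce. Its sample-size calculation concerns 3-month risk and does not enter here.

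**Inputs**
- Contact times of 7 days, 21 days, 3 months and 24 months (Patient follow-up procedures).
- Assumed: true 2-year risk r = 10%, constant hazard; loss L = 10% or 20% over 2 years, unrelated to prognosis.
- Event-free losses are kept in the denominator as non-events. This is one reading of the withdrawal rule.

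**Case 1: events known only to the last scheduled contact**, loss spread evenly.
- Risk by 3 months: 1 − 0.9^(3/24) = 1.31%. Risk by 21 days (0.69 months): 1 − 0.9^(0.69/24) = 0.30%.
- Crude rate = (1 − L) × r + (share lost from 3 to 24 months) × 1.31% + (share lost from 21 days to 3 months) × 0.30%. Losses before day 21 add a negligible amount.
- L = 10%: 9.00% + 8.75% × 1.31% + 0.96% × 0.30% = 9.00% + 0.11% + 0.003% = 9.1%, or 9% relative understatement.
- L = 20%: 8.00% + 17.5% × 1.31% + 1.92% × 0.30% = 8.00% + 0.23% + 0.006% = 8.2%, or 18% relative understatement.
- In simulation, censoring at last contact, with events and event-free time both counted only to that date, gives 10.0% at either loss rate.

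**Case 2: every event before loss is known**, constant hazards λ = −ln(1 − r)/2 and μ = −ln(1 − L)/2 per year.
- Crude rate = λ/(λ + μ) × [1 − (1 − r)(1 − L)].
- L = 10%: 0.500 × (1 − 0.81) = 9.5%, or 5% relative.
- L = 20%: 0.321 × (1 − 0.72) = 9.0%, or 10% relative.
- The relative error is almost the same for true risks of 5% to 20%.

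**Dropping event-free losses instead** reverses the sign. Rate = crude / [crude + (1 − r)(1 − L)].
- Case 2: 9.5/(9.5 + 81) = 10.5% and 9.0/(9.0 + 72) = 11.1%.
- Case 1: 9.1/(9.1 + 81) = 10.1% and 8.2/(8.2 + 72) = 10.3%.

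**Arm difference**, losses kept as non-events.
- Equal true risk of 10%, equal loss: no spurious difference.
- Equal true risk, 10% v 20% loss: 9.5 − 9.0 = 0.5 points (case 2) and 9.12 − 8.24 = 0.9 points (case 1).
- True 10% v 5% (5.0 points), case 2: 4.2 points if loss is 20% v 10%, and 5.0 if it is 10% v 20%.

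**3-month composite**, true 5%: loss of 2% to 10% gives 4.95% to 4.75%.

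**Sampling error for scale**, assuming 50 per arm: √(0.1 × 0.9/50) = 4.2 points for one arm, and √2 × 4.2 = 6.0 points for the difference.

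**The case against.** The strongest reply is that the article never says what outcome a withdrawn, lost or dead patient receives. That rule usually sits in the full protocol or analysis plan, which are not shown, so its absence is no finding. Keeping withdrawals in an intention-to-treat analysis is standard. All of this stands. What remains is narrower: the article has itself fixed the population and the test, and a later plan could use observed follow-up time only by departing from that test.

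A reader might infer more, but the documents do not support it:

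- *Deaths are misclassified.* They are not. A patient who dies without VTE stays in the denominator as a non-event in a crude proportion, and is treated the same way in a competing-risk estimate.
- *The Background's 7% to 15% short-term mortality shows heavy loss here.* That figure is for lower-extremity VTE in general. This trial excludes inpatients, proximal DVT, PE and active cancer.
- *The 3-month composite is biased too.* The window is short, all subjects have record review and interview, and VTE-related sudden death is itself an event.

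It can also be argued that censoring barely helps when no contact falls between 3 months and 2 years. That is so only if events after last contact are counted while event-free time is cut at last contact. With both stopped at the same date, the estimate returns to the true value under independent loss.

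The per-protocol analysis excludes withdrawals, but it also discards their observed time and does not cure loss related to prognosis.

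**Conclusion.** The point holds for VTE recurrence at 2 years and should be stated as a possibility. As written, the plan may understate that rate by about 5% to 9% relative at 10% loss and 10% to 18% at 20% loss. The arm difference may be distorted if loss differs by arm. With equal true risks and equal loss, no false difference arises.

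These sizes rest on an assumed constant hazard, assumed loss rates, loss unrelated to prognosis, and event-free withdrawals being counted as non-events. The documents supply none of these, so the claim that patients are misclassified or that rates are biased goes further than the text allows.

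Severity is low. The outcome is secondary in a feasibility pilot, the stated sample-size calculation uses 3-month risk, and a sampling error of about 4 points per arm exceeds the 1 to 2 points at issue. A larger trial that kept the same method would not shrink the bias, but this article does not fix that trial's analysis.

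**What to change.** In Statistical analysis, for VTE recurrence to 2 years:

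- Estimate cumulative incidence by arm, censoring at last contact, with events and event-free time both counted only to that date. Treat non-VTE death as a competing event.
- Report the 2-year risk difference with its 95% confidence interval.
- Keep Fisher's exact test as a supporting analysis.

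In the withdrawal section, say that withdrawn patients contribute follow-up to their last contact.

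Post-thrombotic syndrome is scored at the 2-year review, so censoring does not suit it. Use patients assessed at 2 years as the denominator, and show best-case and worst-case bounds for those not assessed.

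The 3-month composite can stay as planned.

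The cost is slightly more analysis, plus the recording of event and last-contact dates at the 2-year review. The article specifies record review only at 3 months, so these dates cannot be assumed to be available already. Censoring still assumes that loss is unrelated to prognosis, so loss should be reported by arm.

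### The crossover definition catches anticoagulation that the protocol requires after an endpoint, so the per-protocol analysis removes conservative-arm patients because they had a propagation or pulmonary embolism

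*Protocol article*

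**What the plan says.** Five statements in the protocol article bear on this point.

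- **Patient outcome measures.** The 3-month clinical composite is the "combined incidence of thrombus propagation to the popliteal vein, DVT recurrence, development of pulmonary embolism or VTE related sudden death". The primary feasibility outcomes include "recruitment rate for those deemed eligible, allocation crossover and short-term compliance with the study protocol".
- **Patient follow-up procedures.** Propagation to the popliteal vein at any time after randomization "will be considered as proximal extension and result in immediate therapeutic anticoagulation". For embolism: "Any patient diagnosed with pulmonary VTE will receive immediate therapeutic anticoagulation as per current practice". Both rules apply in either arm.
- **Withdrawal, allocation crossover and protocol violation.** A crossover occurs when "patients allocated to conservative treatment are prescribed full dose therapeutic anticoagulation for > 5 days at any stage during 3-month follow-up". In the anticoagulation arm it occurs when therapy is withheld for more than 5 days. Neither clause makes an exception for a change prompted by an endpoint.
- **Statistical analysis, first comparison.** The clinical comparison is for "prevention of the secondary clinical endpoint following the 'intention to treat' principle".
- **Statistical analysis, second comparison.** "A further 'per protocol' analysis of all clinical endpoints will take place excluding all withdrawals, allocation crossovers and protocol violations".

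**The concern.** Read together, these sections make the outcome a reason for exclusion. A group B (conservative) patient whose thrombus reaches the popliteal vein, or who has an embolism, must be anticoagulated. Once that treatment exceeds 5 days the patient is a crossover, and the per-protocol analysis then removes both the patient and the event. A group A patient with the same event is already on anticoagulation, does not cross over by this route, and stays in with the event counted. The selection is therefore on the outcome, and it works in one arm only. This goes beyond the usual worry that per-protocol sets are not comparable, because events are taken out of the numerator by definition.

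Two results are at stake. One is the per-protocol comparison of the clinical composite. The other is the allocation crossover rate, which is meant to show whether patients can be kept on their allocation. Patients who followed their allocation until an endpoint required treatment would be counted as failures to maintain it. The pilot exists to supply planning figures for a definitive trial, so either distortion could carry forward.

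**Working it through.** **Is there an exemption?** I looked for wording that limits crossover to the time before an event, censors at the endpoint, or separates required from off-protocol anticoagulation. The article has none. The crossover clause covers the whole 3-month follow-up, and the exclusion covers all crossovers and all clinical endpoints.

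**Inputs**

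- Risk without treatment: about 5% (Sample size considerations). As a sensitivity value, 7.8% (Background and Table 1, 5/64).
- Risk on anticoagulation: 1% (Sample size considerations). The planned difference is 5% - 1% = 4 points.
- Pilot size: 100 patients (Sample size considerations). No allocation ratio is stated, so 50 per arm is my assumption.
- Duration of anticoagulation after an endpoint: not stated. I assume more than 5 days. Study interventions describes therapeutic anticoagulation as heparin followed by 3 months of oral treatment, which supports this.

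The article gives no figure for the per-protocol set, so there is none to reproduce.

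**Expected events in group B**

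- At 5%: 50 x 0.05 = 2.5. P(at least one) = 1 - 0.95^50 = 0.923.
- At 7.8%: 50 x 0.078 = 3.9. P(at least one) = 1 - (59/64)^50 = 0.983.

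**Per-protocol risk in group B.** Let p be the true risk and f the share of group B events that are treated for more than 5 days and so excluded. The numerator falls from p to p(1 - f) and the denominator from 1 to 1 - pf:

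per-protocol risk = p(1 - f) / (1 - pf)

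With p = 0.05 and group A left at 1%:

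| f | Calculation | Group B per-protocol risk | Risk reduction v 1% |
|---|---|---|---|
| 1.0 | 0 / 0.950 | 0% | -1.0 points |
| 0.9 | 0.005 / 0.955 | 0.5% | -0.5 points |
| 0.8 | 0.010 / 0.960 | 1.0% | 0.0 points |
| 0.5 | 0.025 / 0.975 | 2.6% | +1.6 points |

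At a true 7.8% the same values of f give 0%, 0.8%, 1.7% and 4.1%.

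**Illustration.** With 6/50 v 0/50 events, Fisher's exact test gives p = 0.027 by intention to treat. If all six patients are excluded, the per-protocol table is 0/44 v 0/50, p = 1.0.

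**Effect on the crossover rate.** If every group B event is counted as a crossover, the rate in that arm rises by 2.5/50 = 5 points, and overall by 2.5/100 = 2.5 points. At 7.8% the figures are 7.8 and 3.9 points.

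**After the change proposed below.** Endpoint patients stay in with their event counted. The per-protocol risk in group B is then about 5% and the risk reduction about 4 points, as planned.

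**The case against.** The strongest reply is that little depends on this analysis. The primary endpoints are feasibility measures, the intention-to-treat comparison comes first, and the per-protocol analysis is an additional one to which no decision is tied. In a pilot of 100 patients with about 0.5 expected events in group A (50 x 0.01), neither comparison carries much weight. The three predefined success criteria are incidence, recruitment and protocol violations. Crossover is not among them, and the article names crossovers and violations separately. Even if they were merged, about 2.5 points overall is small against the 25% limit. All of this stands, and it bounds the harm.

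It can also be said that a condensed article leaves per-protocol timing rules to an analysis plan. That is weaker here, because the article itself fixes both the definition and the exclusion, in terms that leave no gap for timing.

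Four stronger readings are tempting and are not supported.

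- A reader might infer that the per-protocol risk in group B must be zero, or that the analysis would favor conservative care whatever the truth. Sudden deaths from thromboembolism are not removed, no section requires anticoagulation for a distal recurrence, and an event in the last days of follow-up may escape the 5-day rule. The result depends on the share excluded.
- A reader might infer that the main clinical comparison is compromised. The intention-to-treat analysis does not use the crossover rule.
- A reader might infer that per-protocol bleeding in group A is biased down. That would follow if therapy were withheld for more than 5 days because of a bleed. No section says that this will happen, and the bleeding outcome includes nuisance bleeds that need not interrupt treatment.
- A reader might infer that the change costs nothing because event and treatment dates are already recorded. The article does not say so.

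**Conclusion.** The point holds for the per-protocol analysis and for the crossover rate. As written, group B patients with a non-fatal popliteal propagation or embolism who are managed as the protocol requires leave the per-protocol set because of that endpoint, while their group A counterparts remain.

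At the planning risks, the 4-point reduction would appear as anything from -1.0 to +1.6 points as the excluded share goes from 100% to 50%. The chance that the pilot has at least one group B event, and so is open to the problem, is 92%. The crossover rate is inflated by up to about 5 points in group B and 2.5 overall.

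These sizes rest on 50 patients per arm, on post-endpoint anticoagulation lasting more than 5 days, and on the assumed excluded shares, none of which the article states. The intention-to-treat result is unaffected, and the bleeding counterpart in group A is a possibility only.

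**What to change.** Change the analysis definitions in three places. Clinical management is unchanged.

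1. **Crossover definition.** Define allocation crossover as a treatment change of more than 5 days that occurs before, and is not made because of, a confirmed clinical endpoint. The relevant endpoints are propagation, recurrence or pulmonary embolism in group B, and in group A a bleed that led to the withholding. Both conditions are needed. If any earlier endpoint were enough, an unrelated later switch would also be excused.
2. **Per-protocol rule.** Keep patients whose first departure from allocation was a response to such an endpoint, and count that event. Exclude only those whose departure came first or was unrelated. This works with the planned Fisher's exact comparison of proportions and needs no censoring.
3. **Reporting.** Show endpoint-driven treatment changes by arm, separately from the crossover rate.

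The cost is a sentence or so in each place. The timing of, and reason for, each treatment change must also be available. The 5-day rule already needs some treatment timing, but the sponsor should confirm that the case report forms capture both. The change should be made before per-protocol results are examined.
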